## 1. Original study protocol and statistical analysis plan

### 1.1 Trial design

This is a prospective, double blind, randomized, self-control, cohort study, designed to compare the differences between unilateral STN stimulation and unilateral GPi stimulation in the same PD patient with symmetric motor symptoms (a left-extremity to right-extremity ratio of less than 0.15 on the UPDRS-Ⅲ in the both off-medication and on-medication states). Participants with advanced PD who had previously undergone combined unilateral STN and contralateral GPi DBS will be screened based on inclusion and exclusion criteria. After recruitment, participants will be comprehensively evaluated under different conditions (acute unilateral GPi turning-on versus acute unilateral STN turning-on in the both off-medication and on-medication states). All participants and trained assessors are blind to the conditions, which are randomly assigned in two continuous days. The study will be carried out under the supervision of the ethical committee of Shanghai Jiao Tong University Ruijin Hospital, and informed consent will be obtained from all participants (see Figure 1).

[figure not shown]

Figure 1 Trial design

### 1.2 Trial population

Participants are recruited from the Departments of Functional Neurosurgery at Ruijin Hospital, Shanghai Jiao Tong University School of Medicine (Shanghai, China).

### 1.3 Patient population and recruitment

We intend to enroll a total of 10 patients. The study will comprise PD patients who have received combined unilateral STN and contralateral GPi DBS.

#### 1.3.1 Inclusion criteria

1. Patients with idiopathic Parkinson's disease
2. Aged between 55 and 75 years, both male and female
3. Patients who have undergone combined unilateral STN and contralateral GPi DBS for more than 2 years
4. A Hoehn-Yahr (H-Y) stage of less than 4 in the off-medication state
5. A left-extremity to right-extremity ratio of less than 0.15 on the Unified Parkinson’s Disease Rating Scale part Ⅲ (UPDRS-Ⅲ) in the both off-medication and on-medication states.

#### 1.3.2 Exclusion criteria

1. History of serious psychosis
2. History of intractable epilepsy (i.e., seizures)
3. Diagnosed by the investigators that patients with severe cardiac, liver and kidney diseases, or other serious health conditions
4. Dementia (A Mini-Mental State Examination (MMSE) score of < 24), inability to comprehend the experimental protocol or voluntarily provide informed consent
5. Lack of cooperation
6. Additional reasons for exclusion at the discretion of the clinical investigator
7. Poorly controlled depression or anxiety
8. Past history of suicidal attempt

#### 1.3.3 Recruitment of participants

Participants will be recruited by phone-call and directly at the department. A well-trained investigator will be responsible for screening all potentially eligible patients based on the eligibility criteria and obtaining the informed consent.

### 1.4 Interventions

#### 1.4.1 Unilateral DBS of the subthalamic nucleus (STN)

To deliver unilateral STN DBS, we will turn off the bilateral stimulation for an hour, and then turn on the unilateral STN DBS. The STN stimulation will be programmed as previous parameter configuration with optimal therapeutic benefits. Participants will be asked to complete a comprehensive set of assessments under unilateral STN stimulation in the off-medication state. One hour after taking regular medication, participants need to complete the second set of assessments in the on-medication state.

#### 1.4.2 Unilateral DBS of the globus pallidus interna (GPi)

To deliver unilateral GPi DBS, we will turn off the bilateral stimulation for an hour, and then turn on the unilateral GPi DBS. The study protocol is identical to the intervention of unilateral STN DBS but it was done on a different day.

#### 1.4.3 Concomitant interventions

Participants will be asked to withhold antiparkinsonian drugs for 12 hours overnight and stay in the off-medication state until they complete the first set of assessments. Participants will be asked to take regular medication for the second set of assessments in the on-medication state. All process will be repeated for contralateral target on the other day. Usage of all drugs will be documented in the Case Report Form (CRF).

### 1.5 Randomization and blinding

Throughout the study, all participants, independent raters/evaluators and statisticians will be blind to the treatment conditions and parameter configurations. Independent raters who are blind to the conditions will be responsible for the conduct of all the assessments. Participants are blind to the treatment conditions. Movement disorders clinician responsible for programming are blind to the study protocol. They are simply told to adjust parameter to optimize therapeutic effects.

Testing sequence of treatment conditions will be randomly assigned in a one-to-one ratio to the scheduled days. Moreover, participants’ hemispheric targets of DBS should be counterbalanced in the left and right side, with half participants having left-STN DBS and half having left-GPi DBS.

### 1.6 Trial outcomes

1. Differences in motor symptoms between two treatment conditions in the on- and off- medication states, as defined by total UPDRS part Ⅲ scores which range from 0 to 132, with higher score indicating more severe motor symptoms.
2. Differences in balance function between two treatment conditions in the on- and off- medication states, as defined by BBS (Burg Balance Scale) scores which range from 0 to 64, with higher score indicating better balance ability.

### 1.7 Data quality and management

Data collection will be restricted to the those meet the eligibility criteria. Participants who withdraw from the study for any reason will be recorded in their medical records and excluded from the data analysis.

#### 1.7.1 Withdrawal and terminate from the study

Participants will be instantly withdrawn from the study in the following conditions:

1. Endangerment of personal safety;
2. Patient lack of compliance;
3. Withdrawal of informed consent;

#### 1.7.2 Handling of missing data

Mean imputation will be used to handle the missing data in the questionnaire. Listwise deletion will be used to handle the missing data that more than 20%. Participant’s specific missing data for one outcome measure will be deleted while his other data can be included in the data analysis, only if the sample size are described in detail.

### 1.8 Statistical considerations

#### 1.8.1 Sample size

The total of 10 patients are expected to be included in this **exploratory** study.

#### 1.8.2 Data analysis

The (nonparametric) Wilcoxon matched-pairs signed-rank test will be used to make pairwise comparisons between treatment conditions. Categorical data will be analyzed with χ2 tests. A p-value < 0.05 will be considered statistically significant.

## 2. Final study protocol and statistical analysis plan

### 2.1 Trial design

This was a prospective double-blind randomized crossover study designed to compare the acute effect of unilateral STN and GPi stimulation on motor symptoms in several patients with PD. Participants with advanced PD who had previously undergone combined unilateral STN and contralateral GPi DBS were screened based on the inclusion and exclusion criteria. Following recruitment, participants were comprehensively evaluated under four randomized, double-blind conditions: (1) Med−STN+GPi−, (2) Med−STN−GPi+, (3) Med+STN+GPi−, and (4) Med+STN−GPi+. The symbol + means on, while − means off. The **intervention** section explains the details of these conditions. All participants and trained assessors were blinded to the conditions, and patients were randomly assessed over the course of two continuous days. (**Figure. 1**)

[figure not shown]

Figure. 1 Trial design.

### 2.2 Patients

Participants were recruited from the Department of Functional Neurosurgery at Ruijin Hospital, Shanghai Jiao Tong University School of Medicine (Shanghai, China). A total of 10 patients with PD underwent combined unilateral STN and contralateral GPi DBS from September 2017 to September 2018. Following recruitment in April 2020 and screening, eight patients who had received the surgery for 2 to 3 years were included in this study. The inclusion criteria were: 1) diagnosis of idiopathic PD; 2) age between 55 and 75 years, both male and female; 3) treatment with combined unilateral STN and contralateral GPi DBS for 2 to 3 years and with optimal parameters for 3 months; and 4) a Hoehn-Yahr (H-Y) stage of less than 4 in the medication-off state. The exclusion criteria were: 1) history of serious psychosis; 2) history of intractable epilepsy (i.e., seizures); 3) diagnosis of severe cardiac, liver or kidney diseases, or other serious health conditions; 4) dementia (A Mini-Mental State Examination score of <24), inability to comprehend the experimental protocol or voluntarily provide informed consent; 5) lack of cooperation; 6) poorly controlled depression or anxiety. The patients in this study overlapped partly with those in our previous study published in 2020;^5^ those were, patients, 3, 7 and 8. Additionally, according to the asymmetry index, patients were divided into a symmetric group (asymmetry index <0.15, both Med− and Med+ conditions before surgery) and an asymmetric group (asymmetry index ≥0.15, either Med− or Med+ conditions before surgery), and the corresponding subgroup analysis was performed. The asymmetry index was a left-extremity to right-extremity ratio in the MDS UPDRS-III, which was calculated using the formula (left extremity – right extremity) / (left extremity + right extremity). A team of experienced multidisciplinary DBS specialists made the clinical decision regarding the specific DBS target to be used in each patient. That was, unilateral STN DBS was applied to treat the more severe side since we hypothesized that STN is more effective than GPi.

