### 2.6 Data analysis

There were two types of comparisons conducted in this study. The first was the comparison between unilateral STN+ and GPi+ within the same patient group in Med− and Med+ conditions, and the second was the comparison between asymmetric and symmetric groups for the different patient groups in the same condition. Before the comparisons, the Shapiro-Wilk test was used to test the normality of data in each group, yielding the W statistic and *P*-value reflecting the evaluation criteria of distribution. For normally distributed data, a parametric test of the Student’s t-test was used to assess the difference between groups. For the non-normally distributed data, the non-parametric Wilcoxon test was applied to compare the differences. The first comparison mentioned was based on the paired Student’s t-test and Wilcoxon signed-rank test. The second comparison was based on the independent Student’s t-test and Wilcoxon rank-sum test. All three tests mentioned were two-tailed tests with a *P*-value*<0.05* reflective of statistical significance. Statistical calculations and techniques were performed using R-4.0.2.

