## 3. Summary of changes and reasons

| **Original study protocol and statistical analysis plan** | **Changes** | **Reasons** |
| --- | --- | --- |
| We originally intended to enroll a total of 10 patients with a left-extremity to right-extremity ratio of less than 0.15 on the MDS UPDRS-III in the both Med on and Med off states. | We modified the previous requirement of an asymmetry index less than 0.15 in the inclusion criteria.  8 patients were eventually enrolled, only half of whom met the asymmetry index of less than 0.15. | DBS treatment with asymmetric targets was firstly used mainly in patients with asymmetric motor symptoms in both limbs in the pilot study. A total of 10 patients met the requirement of a 2- to 3-year follow-up period, but only 8 patients could be included based on the inclusion criteria and patient preference. |
| We originally intended to perform stimulation parameter adjustments prior to assessments. | In practice, we kept the optimal parameters and did not adjust them before the assessment. | Retaining the stable optimal parameters allows a better comparison of the two targets in daily treatment. |
| We originally intended to perform the assessment in the Med on condition 45 minutes after taking the parkinsonism drugs. | In practice, the assessment in Med on condition was performed 1 hour after taking the medication. | Previous evidence suggests that 1 hour may be more reasonable and that the patient is in a better state. |
| The Wilcoxon matched-pairs signed-rank test and χ2 test were considered to be used. | the Shapiro-Wilk test was used to test the normality of data in each group, yielding the W statistic and *P*-value reflecting the evaluation criteria of distribution. For normally distributed data, a parametric test of the Student’s t-test was used to assess the difference between groups. For the non-normally distributed data, the non-parametric Wilcoxon test was applied to compare the differences. | The final statistical analysis is more standardized. |

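### Asymmetry is tested only as four against four patients after a cut at 0.15; under a linear relation a slope on the continuous index would have more power, by an amount that rests on assumptions

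*Supplement*

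**What the plan says.** Section 2.2 of the final plan defines the asymmetry index from left and right extremity scores on the MDS UPDRS-III as ("left extremity – right extremity) / (left extremity + right extremity"). By this index, "patients were divided into a symmetric group (asymmetry index <0.15, both Med− and Med+ conditions before surgery) and an asymmetric group (asymmetry index ≥0.15"); for the asymmetric group the condition in full is "asymmetry index ≥0.15, either Med− or Med+ conditions before surgery". Each patient therefore gets one label, which is used in both medication states.

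Section 2.6 lists two types of comparison, and "the second was the comparison between asymmetric and symmetric groups for the different patient groups in the same condition". For the tests it says: "The second comparison was based on the independent Student’s t-test and Wilcoxon rank-sum test". Tests are two-tailed at 0.05.

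On numbers, section 2.2 says that "eight patients who had received the surgery for 2 to 3 years were included in this study", and section 3 that "8 patients were eventually enrolled, only half of whom met the asymmetry index of less than 0.15". Half of eight is four, so the comparison is 4 v 4, provided the half counted in section 3 is the half formed by the rule in section 2.2.

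The final plan contains no continuous analysis of the index. It gives no effect size or power for this comparison and no analytic reason for cutting at 0.15.

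**The concern.** Cutting a measured quantity into two groups discards the ordering within each group. Patients just either side of 0.15 count as different, and patients far apart on the same side count as alike. With four patients per group little information is left.

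The rule for combining the two states adds to this. As an illustration, a patient with an index of 0.05 in Med− and 0.16 in Med+ is asymmetric in the Med− comparison, while a patient with 0.14 in both states is symmetric.

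Asymmetry is one of only two types of comparison in section 2.6. At stake is whether the trial can say anything about how the results vary with asymmetry, and whether readers can see how imprecise that evidence is. A bare p-value from 4 v 4 shows neither.

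**Working it through.** **No figure to reproduce.** The plan states no power for this comparison. Everything below is conditional on assumed values.

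**Inputs from the documents:** n = 8 (2.2), split 4:4 (3), two-sided 5% level, independent t-test or rank-sum test (2.6).

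**Assumed inputs:** the correlation rho between index and outcome (0.3 to 0.9), the shape of the index distribution, and the form of the relation.

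**Degrees of freedom.** Slope test: 8 − 2 = 6. Independent t-test: 4 + 4 − 2 = 6. Keeping the index continuous costs none.

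**Rank-sum test.** There are C(8,4) = 70 allocations of ranks. The smallest exact two-sided p is 2/70 = 0.029 and the next is 4/70 = 0.057, so the test rejects only when the groups separate completely. Its true size is about 3%, which explains part of its lower power.

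**Linear relation.** Model: y = rho·x + √(1 − rho²)·e, with x the standardised index and e standard normal. Groups are the lower and upper four by x. There were 100,000 simulated trials per setting. Normal index, power in % (differences taken before rounding):

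| rho | slope | t-test 4 v 4 | loss | rank-sum 4 v 4 | loss |
|---|---|---|---|---|---|
| 0.3 | 10.8 | 8.3 | 2.5 | 4.8 | 6.0 |
| 0.5 | 24.7 | 15.1 | 9.7 | 9.3 | 15.5 |
| 0.7 | 54.7 | 29.0 | 25.6 | 18.9 | 35.7 |
| 0.8 | 75.5 | 40.6 | 34.9 | 27.5 | 48.0 |
| 0.9 | 94.3 | 58.2 | 36.1 | 42.3 | 52.0 |

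At rho = 0 the slope test rejects in 4.9% and the t-test in 5.1%, so the gain does not come from an inflated error rate.

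**Other index shapes, loss in points:**

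| index | t-test, rho 0.3 | t-test, rho 0.5–0.9 | rank-sum, rho 0.5–0.9 |
|---|---|---|---|
| uniform | 2.2 | 8.2–30.9 | 14.8–46.7 |
| half-normal (absolute index) | 2.8 | 10.0–37.0 | 15.6–51.0 |
| exponential (skewed) | 3.3 | 11.6–44.3 | 16.3–52.9 |

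The range of 8 to 37 points covers the uniform, normal and half-normal cases; a strongly skewed index goes above it. Comparing Spearman with the rank-sum test gives a loss of 7.8 to 40.3 points for rho 0.5 to 0.9.

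**Step instead of line.** If the outcome jumps at the cut and is otherwise unrelated to a half-normal index, the split wins:

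| step (SD) | slope | t-test | rank-sum |
|---|---|---|---|
| 1 | 13.8 | 22.5 | 14.2 |
| 2 | 33.3 | 65.7 | 48.9 |
| 3 | 50.4 | 93.9 | 83.1 |

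**The both/either rule.** Grouping on both states amounts to grouping on the larger of the two absolute indices. Assume a correlation of 0.6 between the two signed indices and an outcome linear in the absolute Med− index. The t-test then has 10.4%, 16.1% and 26.6% power at rho 0.5, 0.7 and 0.9. Splitting on the Med− index alone gives 14.7%, 27.6% and 55.7%. The rule costs a further 4.3, 11.5 and 29.1 points. This depends on the assumed 0.6, and it would not hold if the outcome depended on the worse of the two states.

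The choice between t-test and rank-sum by the Shapiro-Wilk test was not modelled.

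**The case against.** **The size is not a property of this trial.** A reader might infer that the cut costs 8 to 37 points of power here. The documents do not support that: they give neither a correlation nor the distribution of the index. At rho 0.3 the loss is 2 to 3 points, and under a step it reverses. A scatter plot and a Spearman check would show a departure from linearity but would not restore the power lost under a step. This stands, and the figure must carry its conditions.

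**The cut is not arbitrary.** A reader might take 0.15 for a convenient or data-driven number. It is the symmetry criterion of the original protocol (1.1 and 1.3.1), including its requirement in both states, and section 3 explains why it was dropped as an entry condition. The symmetric group is thus the population first intended. That justifies describing the group. It does not make a two-group test the best way to ask how asymmetry relates to outcome.

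**A slope may reflect side allocation.** Section 2.2 says STN stimulation went to the more severe side. Suppose limb scores are S (worse side) and M, and each target lowers its contralateral limb score by the same fraction f. Then STN minus GPi is [(1 − f)S + M] − [S + (1 − f)M] = −f(S − M), which is −f × absolute index × (S + M). The difference varies with the index although the targets work equally well. This stands as a limit on interpretation. A 4 v 4 split of the same difference shares it.

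**The outcome would change too.** Section 2.6 compares groups within a condition; regressing the STN-minus-GPi difference is a different question. This stands: the two changes are separate, and the power figures concern only the handling of the index.

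**The consequence is limited.** The primary outcome (2.5) is the within-patient comparison, which the cut does not touch. Nor do the documents say that a non-significant group difference would be read as absence of a relation; that is a risk, not a stated intention.

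**Conclusion.** The point holds in conditional form. The final plan reduces a continuous index to one two-level label for both medication states, tests it only as four against four, and has no continuous analysis. Under a linear relation this loses power at no saving in degrees of freedom: about 2 to 3 points against the t-test at rho 0.3 and about 8 to 37 at rho 0.5 to 0.9 (uniform, normal or half-normal index), and more against the rank-sum test. A true step at 0.15 would favour the split, but the plan does not posit one.

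The alternative is better, not strong: about 25% power at rho 0.5 and 55% at rho 0.7. Neither analysis could support a claim that asymmetry has no effect. This is a worthwhile, inexpensive improvement to a subgroup analysis; it does not undermine the trial's main comparison.

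**What to change.** In section 2.6, replace the asymmetric-versus-symmetric test with a linear regression on the absolute pre-surgery asymmetry index, one model per medication state using the index from that state. The absolute value has to be written down because the formula in 2.2 is signed. Report the slope with its 95% CI, a scatter plot of the eight points, and a Spearman correlation as a check. Keep the 0.15 grouping as a descriptive table, identified as the original protocol's symmetry criterion.

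Decide separately, and state, whether the outcome is the score in each condition or the STN-minus-GPi difference.

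State the limits beside the result: linearity is assumed, one extreme index value can dominate at n = 8, power is low, and the slope may partly reflect placement of STN on the more severe side. Label the analysis exploratory, and post hoc if it is added after the data have been seen.

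The cost is a paragraph of plan text and a few lines of R on indices already needed for the grouping. No new patients, visits or measurements are required.

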### 2.5 Trial outcomes

Acute turning-on effects of unilateral STN stimulation versus unilateral GPi stimulation on motor symptoms in each patient were compared as the primary outcome. Motor symptoms were defined by the MDS UPDRS-III scores which ranged from 0 to 132, with higher scores indicating more severe motor symptoms. To gain insight into the specific effects of each target, we classified the MDS UPDRS-III subscales into three categories: 1) axial signs, as measured by scores on speech, facial expression, arising from a chair, posture, gait, freezing of gait, and posture stability; scores could range from 0 (no axial signs) to 28 (severe axial signs); 2) STN-stimulated contralateral limb symptoms; and 3) GPi-stimulated contralateral limb symptoms. Limb symptom severity was measured using the subscale scores of the corresponding limb on rigidity, finger tapping, hand movements, hand pronation supination, toe-tapping, leg agility, posture tremor, kinetic tremor, and resting tremor amplitude; scores could range from 0 (no limb symptoms) to 52 (severe limb symptoms). The Berg Balance Scale (BBS) was also compared as a second outcome at the 2- to 3-year follow-up. The patient’s daily dose of antiparkinsonian medication was converted into a levodopa equivalent daily dose (LEDD).

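### The asymmetry index is signed but cut on one side only at 0.15, so as written a markedly right-dominant patient can be classed as symmetric while the mirror-image left-dominant patient is classed as asymmetric

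*Supplement*

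**What the plan says.** Section 2.2 (Patients) of the final protocol says that the index was "calculated using the formula (left extremity – right extremity) / (left extremity + right extremity". The same sentence also describes it in words as a ratio of the left to the right extremity.

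The grouping rule in that section has two halves:

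- "symmetric group (asymmetry index <0.15, both Med− and Med+ conditions before surgery"
- "asymmetric group (asymmetry index ≥0.15, either Med− or Med+ conditions before surgery"

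Section 2.2 adds that a subgroup analysis was done on these groups. Section 2.6 (Data analysis) makes the grouping the basis of one of its two types of comparison: "the second was the comparison between asymmetric and symmetric groups for the different patient groups in the same condition".

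Section 3 (Summary of changes and reasons) reports the resulting split: "8 patients were eventually enrolled, only half of whom met the asymmetry index of less than 0.15".

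**The concern.** A measure of symmetry should give the same answer when left and right are exchanged. This one does not. The formula runs from −1 to +1, and the cut-off bounds only the positive end. No place in the current text supplies an absolute value, a lower bound of −0.15, or a worse-minus-better definition. Marked right dominance gives a large negative number, which satisfies the condition for symmetry.

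The verbal description does not help. The formula is not a ratio of left to right, and a literal ratio below 0.15 would mean extreme asymmetry.

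At stake is who belongs to which group in the subgroup analysis and in the between-group comparison. Section 2.2 also says that the STN target was used for the more severe side. In patients with marked asymmetry, target and baseline severity therefore go together, and placing such a patient in the symmetric group would blur the contrast that the grouping is there to draw.

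**Working it through.** **Inputs**

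- Index: AI = (L − R) / (L + R), from section 2.2.
- Rule: symmetric if AI < 0.15 in both medication states, asymmetric if AI ≥ 0.15 in either, from section 2.2.
- Patients: 8, half of them below the cut-off, from section 3.
- Score range: section 2.5 (Trial outcomes) says of the limb outcome that "scores could range from 0 (no limb symptoms) to 52 (severe limb symptoms". Taking 0 to 52 as the range of L and R in the index is an assumption, used only in step 4.

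**1. The plan's own figure.** The split of four and four cannot be reproduced, because the supplement gives no left and right scores per patient. It fits either reading of the index.

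**2. Worked cases**, with the rule as written and with the absolute value of AI in its place:

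| Med− (L, R) | Med+ (L, R) | AI Med− | AI Med+ | As written | Absolute value |
|---|---|---|---|---|---|
| 10, 30 | 5, 15 | −0.50 | −0.50 | symmetric | asymmetric |
| 30, 10 | 15, 5 | +0.50 | +0.50 | asymmetric | asymmetric |
| 0, 52 | 0, 52 | −1.00 | −1.00 | symmetric | asymmetric |
| 20, 22 | 10, 11 | −0.048 | −0.048 | symmetric | symmetric |
| 10, 30 | 12, 8 | −0.50 | +0.20 | asymmetric | asymmetric |

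For example, (10 − 30) / (10 + 30) = −20/40 = −0.50, and (12 − 8) / (12 + 8) = 4/20 = +0.20.

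Rows 1 and 2 are mirror images and fall in different groups. Row 4 shows that a mildly right-worse patient is rightly called symmetric. Row 5 shows that a right-worse patient is still called asymmetric if the other medication state reaches +0.15.

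**3. What the cut-off means.** AI = 0.15 corresponds to L/R = 1.15/0.85 = 1.35. The rule treats the left side being about 1.35 times the right as asymmetric, but sets no limit in the other direction.

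**4. Extent over the assumed score range.** Take all whole-number pairs from 0 to 52, with the same scores in both states. There are 53 × 52 / 2 = 1,378 pairs with the right side worse and 1,378 mirror pairs with the left side worse.

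| | Symmetric as written | Asymmetric as written | Absolute AI ≥ 0.15 |
|---|---|---|---|
| Right worse (1,378) | 1,378 | 0 | 1,045 |
| Left worse (1,378) | 333 | 1,045 | 1,045 |

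So 1,045 right-worse pairs that pass the plan's own threshold in size are called symmetric. These are counts of possible score pairs, not of patients. The direction of the result does not depend on the range, since R > L always gives a negative index.

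**5. Direction of any error.** The absolute value of AI is never smaller than AI. Replacing one by the other can therefore move patients only from symmetric to asymmetric. Anyone classed as asymmetric under the written rule stays so.

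**6. Weight of one patient.** With groups of four, one patient is 1/4 = 25% of a group. If the between-group test is the exact two-sided rank-sum test without ties, there are 70 ways to allot four ranks out of eight. Only complete separation reaches P < 0.05: 2/70 = 0.029, and the next value is 4/70 = 0.057. One misplaced patient could decide the result.

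**The case against.** The strongest reply is that this is a slip in notation. The groups are named symmetric and asymmetric, labels that make sense only if side does not matter, and section 2.2 reports a grouping already done. The investigators may well have used the absolute value and left it out of the text. That is plausible, and nothing in the supplement contradicts it. It does not repair the written rule, which is the only record in the supplement of how the groups were formed.

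The second reply is about reach. The primary outcome in section 2.5 is the within-patient comparison of the two targets, and for the whole cohort that test does not involve the index. The final protocol also no longer uses the index for eligibility. What remains is the subgroup analysis and the second type of comparison in section 2.6, with about four patients per group, and these are weak analyses under either formula. This stands and limits the weight of the point.

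The third reply is that the description as a ratio is only loose wording, since the formula stands in the same sentence. This also stands: the wording should go, but it has no analytic consequence of its own.

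A reader might go further and infer that every right-worse patient is classed as symmetric, or that the asymmetric group holds only left-dominant patients. The two-state rule does not support that, as rows 4 and 5 of the worked cases show.

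**Conclusion.** The rule as written is wrong. It misclassifies a patient whose right side is worse by 0.15 or more on the index in at least one medication state and whose index stays below +0.15 in the other. Such a patient is called symmetric, at values down to −1.00, while the mirror-image patient is called asymmetric.

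The effect is confined to the subgroup analysis and the asymmetric-versus-symmetric comparison. The whole-cohort comparison of STN with GPi stimulation is untouched.

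A reader might conclude that the symmetric group in this trial was in fact contaminated, or that a given share of the asymmetric patients was misplaced. The documents do not support either. They give no per-patient scores by side and do not say how many patients were right-dominant. If the formula was applied literally, between none and all of the four patients below the cut-off could move to the asymmetric group. If the absolute value was used, the split stands and only the text is at fault.

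The finding on the rule rests on the printed formula and cut-off alone. The assumed range of 0 to 52 affects only the counts in step 4, and the rank-sum figures assume groups of four without ties.

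**What to change.** In section 2.2, define the index as |left − right| / (left + right), keep the grouping rule as it is, and delete the description of the index as a left-to-right ratio.

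Then confirm from the pre-surgery left and right scores, in both medication states, that the eight patients were grouped on this definition, and say so. If they were, no result changes. If they were not, re-form the groups and repeat the subgroup analysis and the between-group tests of section 2.6.

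The cost is one formula and a check of sixteen index values (eight patients in two states) from data already in hand. Re-analysis is needed only if the check fails.
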